### Participants

(i) Professionals: Osakidetza PC physicians willing to be involved in a process focused on the optimization of CVD primary prevention; and (ii) patients: all women aged 45–74 years and men aged 40–74 years with hypercholesterolemia but without diagnosed ischemic heart or cardiovascular disease and with a low estimated CVD Risk (< 5%) according to REGICOR who attend at least one appointment at the collaborating PC practices during the study period. Informed consent of PC physicians as representatives of the clusters will be obtained prior to trial commencement.

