#### Adoption

Percentage of FPs out of the total addressed to participate that collaborate in a process to optimize CVD primary prevention practice; characteristics of those participating/not-participating.

Percentage of FPs who change their CVD prevention practice by reducing low-value statin prescribing and increasing health promotion actions in the target population at risk of receiving CVD prevention, 12 months after exposure of physicians to the compared de-implementation strategies.

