### Analysis

Frequencies and proportions along with their corresponding 95% confidence intervals (CIs) will be used to describe the prevalence and the incidence of low-value pharmacological prescribing of statins in primary prevention of CVD of PC professionals (2018 prescriptions being used as the reference level). Factors associated with inappropriate prescribing of statins will be analyzed through stratified statistical analysis and fitting linear logistic models. Given the three levels involved (patients, clinicians, and health organizations), the average variability and possible associated factors will be estimated using hierarchical models and models based on Bayesian estimators.

The primary outcome will be the incidence of new inappropriate prescriptions of statins in patients of the target population (hypercholesterolemic patients without past or current CVD and with an estimated 10-year cardiovascular risk < 5%) 12 months after exposure of physicians to the compared de-implementation strategies. Therefore, to evaluate the impact of the alternative de-implementation strategies, the relative risk of receiving an inappropriate prescription of statins in patients in the target population of the experimental intervention over that of patients from the reference/control group will be estimated by intention-to-treat. Change in new inappropriate prescription incidence rates from baseline to those observed 12 months after physicians’ exposure to the de-implementation strategies and the relative risk reduction ratio will be estimated with the corresponding 95% confidence intervals. In order to adjust for potential confounding factors, stratified statistical analyses and logistic models will be used. These models will be extended to generalized mixed-effects models to take into account the hierarchical structure of data (patients nested in physicians and physicians in PC teams or specialized care services), with fixed effects (comparison group, effect of time on outcome indicators, and time-group interaction) and random effects on the intercept and the time slope (for each patient, physician, center, etc.). These models will be adjusted for potential confounding variables, following a “forward” strategy guided by the stratified analyses. A similar analytic strategy will be followed for secondary outcomes. The analyses will be carried out with SAS, Stata, and R.

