Based on (i) a baseline incidence of 2.7% of new inappropriate statin prescriptions estimated among the patients of the target population seen in 2018 by physicians with an inadequate prescription incidence > 0% with a minimum cluster size n ≥ 20 patients, (ii) an intra-class correlation coefficient of 0.01, (iii) an average cluster size of 56 patients with a coefficient of variation of 0.43, (iv) α = 0.05 and statistical power of 80%, and (v) a hypothetical reduction in annual inappropriate prescription rates in the intervention group of 1.7% in absolute terms or 63% in relative terms (from 2.7 to 1%), the interventional phase will require two study groups with at least 22 physicians each, i.e., at least 44 PC physicians.

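### The 2.7% planning incidence comes only from physicians with at least one event in 2018, a restriction that eligibility does not carry, so the stated 80% power is too favourable

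*Protocol article*

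**What the plan says.** The last paragraph of Analysis in the protocol article bases the sample size on "a baseline incidence of 2.7% of new inappropriate statin prescriptions estimated among the patients of the target population seen in 2018". The rate covers only patients "seen in 2018 by physicians with an inadequate prescription incidence" above zero; the full condition is "by physicians with an inadequate prescription incidence > 0% with a minimum cluster size n ≥ 20 patients". The other inputs are "an intra-class correlation coefficient of 0.01", a mean cluster size of 56 with coefficient of variation 0.43, alpha 0.05 (sidedness not given), power 80%, and a fall from 2.7% to 1.0%. The result is at least 22 physicians per arm, 44 in all.

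Participants describes the professionals to be enrolled as "Osakidetza PC physicians willing to be involved in a process focused on the optimization of CVD primary prevention". It sets no minimum for prior inappropriate prescribing, and neither does Randomization, which allocates physicians once they have consented. The article gives no correction or sensitivity analysis for the difference between the two populations.

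**The concern.** The planning rate concerns the trial's own primary outcome, and it was computed after removing every physician whose observed count was zero. That is conditioning on the outcome. With 56 patients at 2.7%, a physician expects 56 × 0.027 = 1.5 events a year, so zero is an ordinary chance result and not the mark of a distinct group of non-prescribers. If the trial then enrols physicians regardless of past events, its control rate should sit below 2.7%. The same 44 physicians would yield fewer events, and the power claim would not hold.

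The condition of at least 20 patients is different. It is not selection on the outcome and is not part of this point, although it does affect the mean cluster size and should match whatever is enrolled.

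**Working it through.** **Inputs.** All from the sample-size paragraph in Analysis: p1 = 0.027, p2 = 0.010, ICC = 0.01, m = 56, CV = 0.43, alpha 0.05, power 80%, 22 physicians per arm.

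**Step 1: reproduce the plan's figure.**
- Design effect: 1 + [(1 + CV²)m − 1] × ICC = 1 + [(1.1849 × 56) − 1] × 0.01 = 1.654.
- Patients per arm without clustering: {z_α√[2p̄(1−p̄)] + z_β√[p1(1−p1) + p2(1−p2)]}² / (p1 − p2)², with p̄ the mean of p1 and p2. This gives 776 one-sided and 986 two-sided.
- Physicians per arm: 776 × 1.654 / 56 = 22.9 one-sided; 986 × 1.654 / 56 = 29.1 two-sided.
- Power at 22 per arm (effective size 22 × 56 / 1.654 = 745 per arm): 78.6% one-sided, 68.3% two-sided.

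The stated 22 is therefore roughly reproduced one-sided only. Sidedness is a separate question, so each comparison below stays on one basis.

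**Step 2: direction, without a model.** If zero-incidence physicians hold a share s of target patients, the all-physician rate is 2.7% × (1 − s): 2.43% at s = 10%, 2.16% at 20%, 1.89% at 30%, 1.35% at 50%. The document does not give s.

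**Step 3: size, under an assumed model.** Assumptions: list sizes gamma with mean 56 and CV 0.43, cut at 20 or more; events beta-binomial within physician. Solve for the all-physician rate that yields 2.7% among physicians with at least one event.

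| ICC | Physicians with zero events | All-physician rate | Next-year rate, physicians selected on events |
|---|---|---|---|
| 0 | 38% | 1.8% | 1.8% |
| 0.005 | 48% | 1.5% | 1.8% |
| 0.01 | 60% | 1.2% | 1.8% |

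The last column answers the case in which only physicians with events are recruited. They were picked on a noisy count, so their rate in the next year falls back.

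**Step 4: power at 22 per arm.** The 63% relative reduction and the plan's design effect of 1.654 are kept.

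| Control rate → intervention rate | One-sided | Two-sided | Physicians per arm for 80% (one- / two-sided) |
|---|---|---|---|
| 2.7% → 1.00% | 78.6% | 68.3% | 23 / 30 |
| 1.8% → 0.67% | 63.2% | 50.9% | 35 / 44 |
| 1.2% → 0.44% | 48.8% | 36.5% | 53 / 67 |

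Like for like, selection costs about 15 points one-sided (17 two-sided) at 1.8%, and about 30 (32) at 1.2%.

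**Step 5: other ways of holding the effect.** If the intervention arm reaches 1.0% from a 1.8% control rate, power is 37% one-sided and 26% two-sided. If the absolute drop of 1.7 points is kept, power does not fall, but 1.8% would have to go to 0.1%, a 94% reduction (1.7/1.8). From 1.2% that drop cannot occur.

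**Step 6: sensitivity to pairing.** The 1.8% rate with the plan's design effect is a coherent pair for recruited physicians with events at ICC 0.01. For the all-physician rate, 1.8% arises at ICC 0. If the ICC really were 0, 22 × 56 = 1,232 patients per arm would carry no clustering penalty, and one-sided power would be 82% at 1.8% against 93% at 2.7%. The loss from selection remains, but a cautious ICC would then have masked it. The plan's own ICC is 0.01.

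**The case against.** **The size is modelled.** This stands. The document gives neither the share of zero-event physicians nor the all-physician rate, and it does not say in which population the ICC of 0.01 was estimated. Only the direction is certain.

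**The full protocol may restrict recruitment to physicians with events.** It may, and the eligibility mismatch would then go. The 2.7% would still not be rescued, because under the model the next-year rate in those physicians is about 1.8%.

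**Phase II is a feasibility and potential-effectiveness evaluation, its arms and randomization are described as tentative, and 22 and 44 are minimums.** This softens the urgency. The paragraph nevertheless claims 80% power for a stated effect, and that claim should rest on a rate suited to the physicians enrolled.

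**Two stronger readings are tempting and not supported.**
- A reader might set 51% or 37% against the planned 80% and blame the whole gap on selection. Those figures are two-sided, and the two-sided starting point at 2.7% is already 68%. About 12 points of that gap belong to sidedness.
- A reader might infer that "Change in new inappropriate prescription incidence rates from baseline to those observed 12 months after" and "Percentage of FPs who change their CVD prevention practice by reducing low-value statin prescribing and increasing health promotion actions" are contaminated by regression to the mean. That follows only if prior events decide who is recruited, which Participants does not say. If they did, the model gives 54–60% of physicians with fewer events the next year with no effect at all. Even so, regression falls on both randomized arms, and Analysis already makes the main estimate a between-arm relative risk by intention-to-treat with a time-by-group interaction. The treatment comparison is not biased.

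**Conclusion.** The point holds for planning, not for the validity of the comparison. The control rate was estimated in physicians chosen for having an event, the enrolment criteria carry no such condition, and 2.7% is therefore too high for the trial as described. The 80% claim at 22 per arm is not supported. The direction needs no model. The range of 1.2% to 1.8%, and the fall in power to 49–63% one-sided or 37–51% two-sided, rest on the beta-binomial model, the plan's design effect and a constant 63% relative reduction. They show what is plausible and are not estimates from the trial's data. An unattainable 1.7-point drop arises only at the bottom of the range.

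**What to change.** Do one of the following before recruitment:

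1. Re-estimate incidence, mean and CV of cluster size, and ICC in all physicians who meet the trial's eligibility, without conditioning on the outcome. The cross-sectional study in Phase I already plans a 2014–2018 extraction with annual incidence overall and by physician, so the data are to hand.
2. If physicians with prior events are the intended target, write that restriction into Participants, select on one year (for example 2017) and estimate the rate in the next (2018).

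Then restate the number of physicians, the power or the detectable difference, and state the population behind each input. Only if prior events are used for recruitment: do not use the selection year as the baseline for the change in incidence or for the share of physicians who reduce prescribing, and read both as between-arm contrasts.

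The cost is a re-run on planned data, a few sentences of text, and either more physicians or a less favourable stated power.

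### The 22 physicians per arm fits only a one-sided 5% test that the protocol never declares; at two-sided 5% the inputs need 29 to 30, and 44 physicians give about 68% power

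*Protocol article*

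**What the plan says.** The sample-size paragraph closes the Analysis section of the protocol article. It takes "a baseline incidence of 2.7% of new inappropriate statin prescriptions", a hypothesised fall of "1.7% in absolute terms or 63% in relative terms (from 2.7 to 1" per cent), "an intra-class correlation coefficient of 0.01", "an average cluster size of 56 patients with a coefficient of variation of 0.43", and "α = 0.05 and statistical power of 80" per cent. From these it concludes that "the interventional phase will require two study groups with at least 22 physicians each, i.e., at least 44 PC physicians". It does not give the sidedness of α or the formula used.

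Earlier in the same section, the primary comparison is described as a relative risk by intention to treat. For the change in incidence rates it says that this and "the relative risk reduction ratio will be estimated with the corresponding 95% confidence intervals". No one-sided test or one-sided interval is mentioned anywhere in the article.

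**The concern.** Every input that a standard cluster-trial calculation needs is given, apart from the sidedness. With α = 0.05 read in the usual two-sided way, the inputs lead to a clearly larger number of physicians than 22. This is the only sample-size justification in the article, and it serves the primary outcome. If the two-sided reading applies, a trial at the stated minimum has roughly a one-in-three chance of missing the effect it was planned to find, where the article implies one in five. A null result would then be given more weight than it deserves.

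**Working it through.** **Inputs** (all from the sample-size paragraph of the Analysis section): p₁ = 0.027, p₂ = 0.010, difference 0.017, ICC 0.01, mean cluster size m = 56, CV 0.43, α = 0.05, power 80%, 22 physicians per arm.

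**Design effects**
- Ignoring the CV: 1 + (56 − 1) × 0.01 = 1.55.
- With the CV: 1 + [(1 + 0.43²) × 56 − 1] × 0.01 = 1 + (66.354 − 1) × 0.01 = 1.654.

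**Individually randomised size per arm**, unpooled variance: n = (z_α + z_β)² × [p₁(1 − p₁) + p₂(1 − p₂)] / (p₁ − p₂)². The variance sum is 0.026271 + 0.009900 = 0.036171, and 0.017² = 0.000289.

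**Step 1: reproducing the stated 22 (one-sided 5%)**
- (1.645 + 0.842)² = 6.183, so n = 6.183 × 0.036171 / 0.000289 = 774.
- Without the CV: 774 × 1.55 / 56 = 21.4. The pooled-variance form gives 21.5. Both round up to 22.
- With the CV: 774 × 1.654 / 56 = 22.9, which rounds up to 23.
- Arcsine formula with the CV: 734 × 1.654 / 56 = 21.7, which rounds up to 22.

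So 22 is recovered at one-sided 5%, either by leaving out the CV that the paragraph lists or by using the arcsine formula, which it does not mention.

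**Step 2: the same inputs at two-sided 5%**
- (1.960 + 0.842)² = 7.849, so n = 7.849 × 0.036171 / 0.000289 = 982.
- With the CV: 982 × 1.654 = 1,624 patients, and 1,624 / 56 = 29.0 physicians per arm. The unrounded value is 29.007, so strict rounding up gives 30. The pooled form gives 29.1, also 30.
- Without the CV: 982 × 1.55 / 56 = 27.2, which rounds up to 28.

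**Step 3: other two-sided formulas**

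| Formula | No CV | With CV |
|---|---|---|
| Unpooled | 27.2 | 29.0 |
| Arcsine | 25.8 | 27.5 |
| Log relative risk | 29.7 | 31.7 |
| Log odds ratio | 29.6 | 31.6 |
| Continuity-corrected | 30.5 | 32.5 |

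A formula built on a between-cluster CV of 0.60 (derived from the ICC at 2.7%) gives 25.7 without the CV of cluster size, or 26.7 with its usual one extra cluster. The range is therefore about 26 to 33. For 22 per arm to suffice two-sided, the design effect would have to be 22 × 56 / 982 = 1.25. The stated ICC and cluster size give 1.55 to 1.65, and choice of formula or rounding does not close that gap.

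**Step 4: power at 22 per arm, CV applied**
- Effective size per arm: 22 × 56 / 1.654 = 745.
- Standard error of the difference: √(0.036171 / 745) = 0.00697, and 0.017 / 0.00697 = 2.44.
- Two-sided: Φ(2.44 − 1.96) = 68%. A t reference on 42 degrees of freedom gives 66%, and the arcsine form gives 71%. Ignoring the CV, the standard formula gives 71%.
- One-sided: Φ(2.44 − 1.645) = 79%.

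**Step 5: effect detectable with 22 per arm at two-sided 5%**

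80% power is reached for a fall from 2.7% to about 0.80%, a relative reduction of (2.7 − 0.8) / 2.7 = 70%.

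**The case against.** A reader might infer that the stated inputs simply cannot give 22. The document does not support that. It leaves the sidedness open, and Step 1 recovers 22 at one-sided 5%. The planned 95% intervals make a two-sided reading likely but do not prove it: they serve estimation, and no decision rule is attached to them. This part of the objection stands, so the defect is an undeclared sidedness and what follows from it.

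Three further arguments limit the consequence without removing it.

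- **The numbers are a floor.** The article says at least 22 and at least 44, so recruitment may go higher. But it is the floor that carries the 80% claim, and under a two-sided test the floor is too low.
- **The design is tentative.** Phase II is described as a feasibility and potential-effectiveness evaluation, tentatively randomised, with the final design still to be disseminated and a third arm possible. The final size may therefore change. The article nevertheless makes a formal power statement, and that statement should follow from its inputs.
- **The planned models may be more efficient.** The Analysis section foresees time and time-by-group terms and covariate adjustment, whereas 68% refers to an unadjusted post-exposure comparison. The article gives no correlations from which to compute a gain. If a baseline-adjusted analysis with cluster autocorrelation between 0.5 and 1.0 is assumed, power at 22 per arm would be roughly 70% to 76%. That is still below 80%, and a pure change-score analysis could do worse.

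**Conclusion.** The point holds, subject to the sidedness. The figure of 22 per arm is consistent only with a one-sided 5% test. That test is declared nowhere and does not fit the planned 95% intervals, since a one-sided 5% test corresponds to a 90% two-sided interval. Even then, the standard formula with the stated CV gives 23 rather than 22, a minor shortfall.

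Under the conventional two-sided reading the requirement is 29 to 30 physicians per arm, 58 to 60 in total, against a stated minimum of 44. Power at that minimum is about 12 points below the claim. The 68% assumes the stated incidences, ICC and cluster sizes, equal arms, no loss of physicians and an unadjusted comparison. It should not be taken as the power of whichever model is finally fitted.

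The correction should be made, because the stated power governs how a null primary result will be read.

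**What to change.** State the sidedness of α in the sample-size sentence; the rest depends on it.

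- **If two-sided:** give 29 to 30 physicians per arm as the number that matches the inputs. If the minimum stays at 44, restate its power as about 68% for 2.7% against 1%, or say that it gives 80% power for 2.7% against about 0.8%.
- **If one-sided:** declare the test, justify it, and align the reported intervals with it. Add that with the CV applied the standard formula gives 23 per arm, and about 79% power at 22.

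In either case, name the formula and say whether the CV was applied. Restating the figure costs one corrected sentence and a less favourable power claim, with no extra recruitment. Keeping 80% power at two-sided 5% for the stated effect would cost 14 to 16 more physicians (58 to 60 in place of 44).

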## Discussion

The DE-imFAR study aims to provide valid scientific knowledge regarding a structured and theory-informed process for designing and evaluating effective and feasible de-implementation strategies to favor the abandonment of low-value pharmacological prescribing in clinical practice. In brief, the study proposes a detailed systematic process for identifying determinants of low-value practices, identifying behavioral objectives as areas for improvement, designing, and operationalizing de-implementation strategies informed by several theoretical frameworks to target the identified multilevel determinates of low-value practices, and finally, evaluating the feasibility and potential effectiveness of the de-implementation strategies to reduce the low-value practice. Specifically, the present study targets the unnecessary pharmacological prescribing of statins in the primary prevention of CVD in low-risk patients.

There is a growing body of evidence suggesting that the elimination (that is, the de-implementation) of ineffective and potentially harmful clinical practices (i.e., low-value) is essential for the provision of high-quality care and the sustainability of our health system. Nonetheless, such initiatives are being limited to producing lists of candidate practices to be eliminated and/or of what-not-to-do recommendations. The evidence base related to successful de-implementation strategies to eliminate low-value practices is in its infancy.

This study aims to provide valid scientific knowledge in several specific areas related to the de-implementation of low-value practices. First, this is among the first studies applying the most prominent implementation theories and frameworks specific to the field of de-implementation. In doing so, it aims to compare the effectiveness and feasibility of passive dissemination-based interventions with active de-implementation strategies that emerge from a structured and theory-informed process for the design of de-implementation strategies. Second, due to the clinical scenario addressed, the reduction of low-value prescribing of statins in CVD primary prevention where the promotion of healthy lifestyles is the recommended practice, the present project will attempt to shed light on the added effect of replacement with an alternative for the de-implementation of a given low-value care, over reversal without a substitute or alternative. And third and last, the eventual expected impact of this project is to tackle a type of low-value intervention that has a significant impact on health costs for our health system and for patients themselves, thereby contributing to the financial sustainability of the health system. All of this is to be achieved through robust research into new practices and innovations for the optimization of clinicians’ practice and the provision of health services, guided by the emerging science of implementation and de-implementation. If the strategies explored are successful, health planners and managers will have the evidence needed to support the introduction of innovations emerging from research in these innovative fields.

## Data Availability

Since data supporting the present study will mostly concern routine data retrieved from the electronic health records of the Basque Health Service-Osakidetza, it will be only shared on justified request to the study guarantors.

